## Abstract

**Background:**

More than 88 million Americans are at risk of developing type 2 diabetes mellitus (T2DM). The National Diabetes Prevention Program’s Lifestyle Change Program (DPP LCP) has been shown to be effective in reducing the risk of progressing from prediabetes to T2DM. However, most individuals who could benefit from the program do not enroll.

**Objective:**

The aim of this trial is to test the real-world efficacy of 3 mobile phone–based approaches to increasing enrollment in the DPP LCP including a best-practice condition and 2 novel approaches.

**Methods:**

We will conduct a 3-armed randomized clinical trial comparing enrollment and 1-month engagement in the DPP LCP among adults with prediabetes from 2 health care settings. Participants in the best-practice condition will receive SMS-based notifications that they have prediabetes and a link to a website that explains prediabetes, T2DM, and the DPP LCP. This will be followed by a single question survey, “Would you like the DPP LCP to call you to enroll?” Participants in the 2 intervention arms will receive the same best-practice intervention plus either 2 mobile 360° videos or up to 5 brief phone calls from a health coach trained in a motivational coaching approach known as Motivation and Problem Solving (MAPS). We will collect measures of diabetes-related knowledge, beliefs in the controllability of risk for T2DM, risk perceptions for T2DM, and self-efficacy for lifestyle change pre-intervention and 4 weeks later. The primary outcomes of the study are enrollment in the DPP LCP and 4-week engagement in the DPP LCP. In addition, data on the person-hours needed to deliver the interventions as well as participant feedback about the interventions and their acceptability will be collected. Our primary hypotheses are that the 2 novel interventions will lead to higher enrollment and engagement in the DPP LCP than the best-practice intervention. Secondary hypotheses concern the mechanisms of action of the 2 intervention arms: (1) whether changes in risk perception are associated with program enrollment among participants in the mobile 360° video group and (2) whether changes in self-efficacy for lifestyle change are associated with program enrollment among participants in the MAPS coaching group. Finally, exploratory analyses will examine the cost effectiveness and acceptability of the interventions.

**Results:**

The project was funded in September 2020; enrollment began in February 2021 and is expected to continue through July 2022.

**Conclusions:**

We are conducting a test of 2 novel, scalable, mobile phone–based interventions to increase enrollment in the DPP LCP. If effective, they have tremendous potential to be scaled up to help prevent T2DM nationwide.

**Trial Registration:**

ClinicalTrials.gov NCT04746781; https://clinicaltrials.gov/ct2/show/NCT04746781

**International Registered Report Identifier (IRRID):**

DERR1-10.2196/28884

## Introduction

### Background

Among US adults, 34.5% have prediabetes, placing them at increased risk of type 2 diabetes mellitus (T2DM) [1]. Extensive evidence has shown that therapeutic lifestyle changes can reduce the progression from prediabetes to T2DM by 58% [2]. To address this national epidemic, the Centers for Disease Control and Prevention (CDC) has established the National Diabetes Prevention Program’s Lifestyle Change Program (DPP LCP) [3]. However, through 2019, only 0.4% of the 88 million adults in the United States with prediabetes have enrolled in the DPP LCP [4].

There are several reasons for low enrollment and engagement in the DPP LCP. First, many people with prediabetes are unaware of their risk for T2DM or do not believe that they are at risk of developing T2DM or its associated complications. Second, many individuals are not aware of the appropriate lifestyle changes that can prevent progression to T2DM [5-8]. This is important because risk perceptions are predictive of health behavior change [9]. Finally, several studies have identified practical barriers to enrolling in the DPP LCP, including the cost of enrollment, limited time for attendance, and difficulty with travel to and from DPP LCP sessions [10,11].

Most prior research on DPP LCP enrollment interventions has tested the effectiveness of medical providers notifying their patients of their prediabetes, counseling them, and referring them to the DPP LCP. These studies have reported DPP LCP enrollment rates of 8%-11% [12,13]. We believe there are significant limitations to this approach. First many providers do not notify their patients that they have prediabetes — only 15.3% of individuals with prediabetes report being told about their condition from a health professional [1]. Second, many providers do not currently counsel their patients about lifestyle changes, [14,15], likely because they do not feel they have the time or because they do not feel that such counseling will be effective [16,17].

In this project, we propose to address these issues by directly connecting with individuals with prediabetes through mobile phone–based interventions in a 3-armed randomized controlled trial. We will compare a best practice intervention with 2 novel interventions our research group has developed and pilot tested: mobile 360° videos and Motivation and Problem Solving (MAPS)–based phone counseling.

### Aims and Objectives

Aim 1 is to conduct a 3-armed randomized clinical trial comparing enrollment and 1-month engagement in the DPP LCP among adults with prediabetes receiving risk notification and education alone, risk notification and education plus the mobile 360° video, and risk notification and education plus MAPS.

Aim 1.1 is to examine the mechanisms underlying the mobile 360° video by comparing changes in deliberative, experiential, and affective risk perceptions across study arms.

Aim 1.2 is to examine the mechanisms underlying MAPS by comparing changes in DPP LCP–related self-efficacy across study arms.

## Methods

### General Methods

As noted in the previous section, whether an individual enrolls in the DPP LCP is a multifactorial process that includes their awareness, knowledge, risk perception, and unique barriers. Our intervention is designed to address each of the factors. First, to address low awareness of prediabetes, individuals with a diagnosis of prediabetes within the past 5 years documented in their electronic health record (EHR) will be informed via text message that they have prediabetes and sent a link to the website, Do I Have Prediabetes [18], that includes 3 components: a self-assessment of risk, didactic pages about prediabetes and T2DM, and didactic pages about the National DPP LCP and its benefits.

Individuals will then be randomized to receive only the initial best practice intervention, the best practice plus the mobile 360° videos, or the best practice plus MAPS counseling. The proposed mechanism of action for the mobile 360° videos divides risk perceptions into *deliberative* risk perceptions (ie, the individual's estimates of the likelihood of developing a condition), *affective* risk perceptions (ie, the individual's level of worry about a particular risk), and *experiential* risk perceptions (ie, how easy it is to imagine developing a condition). The videos are hypothesized to increase participants' affective (emotional) and experiential (gist-based) risk perceptions and the likelihood of enrolling in the DPP LCP. The proposed mechanisms of action for MAPS counseling include increasing both motivation and self-efficacy (eg, by addressing practical barriers to enrolling and engaging in the National DPP LCP).

The DPP LCP is an evidence-based program that is available at hundreds of locations throughout the United States as well as online [19]. It is a therapeutic lifestyle change program that reduces the risk of progression to T2DM by 58% for high-risk individuals [20]. The year-long lifestyle change program is comprised of weekly group meetings for 6 months followed by monthly meetings for another 6 months (a minimum total of 22 hours over the year) [1].

### Intervention

#### Best Practice Condition

In the best practice condition, we will send a text message to individuals who, according to their health records, have prediabetes. This message will notify them that they have prediabetes and refer them to a website that provides information about prediabetes and the effectiveness of the DPP LCP. This component of the intervention will increase participants’ awareness of the condition and the DPP LCP without adding to the workload of primary care clinicians. Additionally, this is a process that can be automated to regularly reach new individuals with prediabetes within a health system. While it is not yet standard clinical practice to notify individuals with prediabetes of their condition and offer the DPP LCP to them, there is evidence that individuals with prediabetes who are notified about their status are more likely to engage in self-directed healthy lifestyle changes [21]. Additionally, the American Diabetes Association 2018 Standards of Medical Care in Diabetes recommend that all patients with prediabetes “should be referred to an intensive behavioral lifestyle intervention program modeled on the Diabetes Prevention Program.” This recommendation has an evidence level of “A” [22].

#### Mobile 360° Videos

The mobile 360° videos (in which the viewer moves their phone to “look around” the world of the video) are intended to increase individuals’ risk perceptions regarding the potential adverse outcomes that might occur should they develop T2DM. Our team has designed and pilot tested two 3-minute videos with accompanying voiceover (in either English or Spanish) and soundtrack. In the first video (Figure 1A), the narrator describes the effect of diabetes on health and family life as an individual progresses from having prediabetes to T2DM and having a heart attack. The second video (Figure 1B) provides a vicarious experience of the changes in vision that occur as diabetic retinopathy progresses and uses the visual metaphor of building height to change risk perceptions: As the viewer is transported through a cityscape from a roof to progressively higher roofs, they develop visual scotomas that worsen as the height of the buildings (reflecting their average glucose level) increases. Each video ends with a positive message that enrolling in the DPP LCP can reduce the risk of this potential negative future.

**Figure 1 figure1:**
[figure not shown]
Screenshots of mobile 360° videos.

#### MAPS

MAPS is a hybrid counseling technique that combines motivational interviewing and social cognitive, practical problem-solving to enhance motivation and self-efficacy for behavior change. MAPS has been shown to help people effectively participate in evidence-based programs and change their health behaviors [23,24]. Aside from our pilot work (manuscript in progress for the MAPS pilot and manuscript under review for the mobile 360° videos), these interventions had not been previously evaluated as tools to promote the DPP LCP.

A standardized MAPS training and treatment manual has been developed and used in pilot work and will be utilized in this project. Coach training will include both online “classroom” instruction and practice coaching sessions with feedback from a MAPS expert (KL).

The MAPS counseling itself will focus on promoting enrollment and engagement in the DPP LCP by addressing each participant’s unique values and barriers. MAPS uses a combination of motivational enhancement and social cognitive approaches based on motivational interviewing and practical problem-solving approaches. All participants will receive up to 5 telephone counseling calls lasting approximately 10 minutes during the 4 weeks following study enrollment. The timing of the MAPS counseling calls will be negotiated between the participant and health coach, as has been done for other MAPS trials. The MAPS counselor will also help each participant develop an individualized “wellness plan” that may not only include goals related to DPP LCP enrollment and engagement but also other potential stressors and concerns (eg, transportation, interpersonal issues, family problems, financial concerns). Thus, MAPS will assist individuals with various life stressors that may ultimately affect their DPP LCP engagement. MAPS counseling will be conducted via telephone in Spanish or English, and information from each session will be documented in a secure REDCap database.

All MAPS counseling sessions will be audio-recorded, and the recordings will be uploaded into the study database (in REDCap). Ongoing training and monitoring of recorded calls will ensure that the delivered MAPS follows the protocol precisely. A MAPS expert will review at least one recording per coach per week and provide detailed feedback and guidance as necessary to the health coach.

### Setting

Study participants will be recruited from 2 sites: University of Utah Health and the Midvale Community Building Community Clinic (CBC). University of Utah Health is the Mountain West’s only academic health care system and includes 5 hospitals, 12 community clinics, and several specialty centers. The Midvale CBC is an outpatient community health clinic providing medical, dental, physical therapy, and mental health services to low-income and uninsured families, with a predominantly Spanish-speaking clientele.

### Participants

Spanish- and English-speaking patients ages 18-89 years from University of Utah Health and the Midvale CBC will be invited to participate in the study.

#### Inclusion Criteria

Patients will be considered eligible for the proposed trial if (1) they are aged 18-89 years, (2) have a diagnosis of prediabetes within the past 5 years documented in the EHR (ICD-10 code R73.03), and (3) have an email or mailing address and a mobile telephone number on record with the health system.

#### Exclusion Criteria

Patients will be excluded from the study if they have any of the following diagnoses: T2DM (ICD-10-CM E11), type 1 diabetes mellitus (ICD-10-CM Diagnosis E10), diabetes mellitus due to underlying condition (ICD-10 E08), drug or chemical induced diabetes mellitus (ICD-10 E09); gestational diabetes (ICD-10 024.4), neonatal diabetes mellitus (ICD-10 P70.2), or post-pancreatectomy diabetes mellitus (ICD-10 E13). Individuals who are currently pregnant will be excluded from the trial. The rationale for this exclusion is that these women would be excluded from participating in the National DPP LCP. In addition, individuals who do not have an email address or mailing address or who do not own a smartphone will be excluded from the trial, simply because they could not complete the trial.

### Study Design

This is a 3-arm stratified randomized clinical trial comparing enrollment and 1-month engagement in the DPP LCP among adults with prediabetes receiving risk notification and education alone vs risk notification and education plus mobile 360° video vs risk notification and education plus MAPS. It should be noted that this study is not powered nor designed to compare the effectiveness of the mobile 360° videos vs MAPS nor does the design allow for testing of the additive value of mobile 360° videos plus MAPS.

### Procedures

#### Overview

Figure 2 provides an overview of the study procedures. We will begin by pulling lists of potential participants (using the inclusion and exclusion criteria listed in the previous sections) from the EHR of each health system. Selected individuals will be given the option to opt-out of any study-related communication prior to phone contact. Hence, we will first contact potential participants by email (or by letter if they do not have an email address on record) with a brief description of the study and an explanation that they will be contacted on their mobile phone in 2 weeks if they do not opt out. This email will include a link to click if they want to be excluded from further study communication. All further communication will be with individuals who did not opt out and will be sent via SMS messages to their mobile phone.

**Figure 2 figure2:**
[figure not shown]
Overview of study procedures. DPP: Diabetes Prevention Program; MAPS: Motivation and Problem Solving.

#### Screening and Baseline Survey

Potential participants who do not opt-out will then be sent an SMS message with a link to a survey. The survey will begin with a short eligibility screening section. Individuals who are screened out will be thanked for their time and informed that they do not meet the criteria for participating in the study.

Individuals who are not screened out will be directed to the consent cover letter and the remainder of the baseline survey. The baseline survey will collect information about demographics (age, sex, race/ethnicity, education, socioeconomic status), diabetes-related knowledge (11 items), and beliefs about the controllability of risk for type 2 diabetes (4 items) using 2 subscales on the risk perception for developing diabetes scale [25]. It will also collect information on self-efficacy related to DPP LCP participation as well as for diet, exercise, and weight loss (16 items) using the brief self-efficacy scales adapted from Wilson et al [26]. This will be followed by an 18-item scale of risk perceptions for T2DM that includes 6 items each to assess 3 different aspects of risk perception: deliberative, affective, and experiential risk perceptions [27].

#### Allocation to Condition

After completing the baseline survey, individuals will be allocated to the condition according to randomization tables generated by the projects statistician (YZ). These tables will be based on permuted block randomization, stratified by health system and sex, with block sizes randomly generated as 5, 10, or 15. In accordance with our planned sample sizes in each arm, each block will maintain a 1:2:2 ratio in sample size across the treatment groups (best practice, mobile 360° videos, and MAPS).

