### Measures

#### Outcome Measures

The primary outcomes of the study are DPP LCP enrollment and 4-week engagement, as defined by the CDC (Table 1). These data are currently collected by all CDC-recognized organizations offering the National DPP LCP and are a part of their required reporting for DPP LCP recognition.

**Table 1 table1:** Centers for Disease Control and Prevention (CDC)–defined measure of enrollment and engagement in in-person and online Diabetes Prevention Program’s Lifestyle Change Programs (DPP LCPs).

Time point	In-person	Online
Milestone 1 (enrollment)	Registration for the program	Setting their password for the app
Milestone 2 (4-week engagement)	Attending at least 2 out of the first 4 sessions	Must do at least 2 of the following activities: (1) Complete 2 education modules; (2) send at least 1 in-app message and/or Group Wall post; (3) set or log at least 1 behavior; (4) log, plan, or research at least 3 meals; (5) log physical activity at least 3 times; (6) weigh in on 3 or more days during 2 out of the first 4 sessions

The DPP LCP at University of Utah Health is covered by some insurance plans and requires an out-of-pocket fee for those without coverage. The cost for the online program is currently US $504, and the cost for the in-person program is US $425. Some scholarships are available for those who meet income guidelines. These costs may change during the course of the study. The Midvale CBC’s program is offered free of charge and is currently funded by a grant. To minimize the problem of cost as a barrier to enrollment, University of Utah Health participants who are uninsured or underinsured may be invited to participate in the Midvale CBC program. Otherwise, all other participants will only be invited to attend the program offered by their health system.

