We will use logistic regression to compare the effects of the 3 treatments on the likelihood of enrollment and 1-month engagement in the DPP LCP. The distributions of participants’ demographics and baseline measures of risk perception and self-efficacy will be summarized and compared by treatment groups using chi-squared tests for categorical variables and *F* tests for continuous variables. If participants’ demographics and baseline measures of risk perception are not balanced across the 3 treatment groups at baseline, we will use inverse probability of treatment weighting with propensity scores to create a synthetic sample and compare the difference in the causal average treatment effects across the 3 treatment groups [35]. We will calculate standardized differences to check whether the distribution of baseline covariates is independent of treatment groups conditional on the propensity score. We will conduct intention-to-treat analysis to account for noncompliance. We will summarize missing data for all variables in the dataset. We will employ multiple imputation to examine the impact of any missing values in a sensitivity analysis. All analyses will be conducted using statistical programming language R, and statistical significance will be defined at alpha=.05.

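### Randomization is stratified by health system and sex, but the stated primary analysis names neither and its covariate rule would not reliably bring them in; the likely cost is small

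*Protocol article*

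**What the plan says.** Under Allocation to Condition, permuted blocks are "stratified by health system and sex, with block sizes randomly generated as 5, 10, or 15", and "each block will maintain a 1:2:2 ratio in sample size across the treatment groups" (best practice, video, MAPS).

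Under Statistical Analyses, the Aim 1 text opens with this sentence: "We will use logistic regression to compare the effects of the 3 treatments on the likelihood of enrollment and 1-month engagement". No covariate is attached to that model. The same paragraph plans tests of baseline balance. If demographics and baseline risk perception turn out unbalanced, "we will use inverse probability of treatment weighting with propensity scores to create a synthetic sample".

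Screening and Baseline Survey lists the demographics as "demographics (age, sex, race/ethnicity, education, socioeconomic status". Sex is in that list; health system is not.

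On the two programs, Outcome Measures says of University of Utah Health: "The cost for the online program is currently US $504, and the cost for the in-person program is US $425". The Midvale clinic's "program is offered free of charge and is currently funded by a grant". The same paragraph adds that some insurance plans cover the University program, that scholarships exist, and that uninsured or underinsured University patients may be offered the Midvale program.

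**The concern.** Stratified blocks force the arms to be nearly balanced on health system and sex, so differences between strata drop out of the arm comparison. A standard error that ignores the strata still counts those differences as noise. If a stratification factor predicts enrollment, the reported error is then larger than the true one, and the test is a little conservative.

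The stated rule for covariates does not repair this. It makes adjustment depend on observed imbalance. Sex is balanced by design and so is unlikely to trigger the weighting, and health system is not among the variables that could. The rule therefore tends to bypass the two variables that the design singled out.

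Health system is the factor more likely to matter. The Background names cost as a barrier to enrolling, and the two programs differ in cost. At stake are some precision and power for the two primary outcomes, and a data-dependent choice of whether to adjust. The false-positive rate is not inflated.

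**Working it through.** **Inputs from the article.** Arms of 80, 160 and 160; enrollment 2%, 32% and 45%; alpha .05 (taken as two-sided); stratified blocks of 5, 10 or 15 at 1:2:2.

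**Inputs assumed.** The article gives no site shares and no enrollment by site or sex. Midvale share was set at 20% or 50%, the site odds ratio at 1, 2 or 5, and the sex odds ratio at 1.

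**1. The plan's own figure.** For 2% versus 32%, SE = √(0.02×0.98/80 + 0.32×0.68/160) = √(0.000245 + 0.00136) = 0.0401. Then 0.30/0.0401 = 7.5, far above 1.96. Computed power is 0.999999 for 2% versus 32% and 1.000 for 2% versus 45%. The stated power above 99% is reproduced. In simulation at these rates, both models rejected in every run with at least one control enrollee.

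**2. Risk-difference standard error by formula.** Ignoring strata, the variance is p0(1−p0)/80 + p1(1−p1)/160. After stratified allocation, each p(1−p) is replaced by Σ q_s·p_s(1−p_s), where q_s is the share of stratum s.

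Example: 10% versus 25%, equal sites, site odds ratio 5. The site rates are 3.74% and 16.26% in control, and 11.24% and 38.76% in the intervention arm.
- Ignoring strata: 0.09/80 + 0.1875/160 = 0.002297, SE 0.0479.
- With strata: 0.0861/80 + 0.1686/160 = 0.002130, SE 0.0461.
- Ratio 1.039, an overstatement of about 4%.

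Across the rates examined (2% vs 32%, 2% vs 45%, 10% vs 10%, 20% vs 20%, 10% vs 25%) and both shares, the overstatement is about 2–7% at a site odds ratio of 5 and about 0.5–1.3% at 2. It is zero at 1.

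**3. Simulation** (1,500 runs per scenario, N = 400, stratified blocks; arm alone versus arm + site + sex).
- Risk difference, site odds ratio 5: model SE exceeds empirical SD by roughly 0–8%, in line with step 2. The highest values come from the design rates, where runs without control enrollees were dropped and the ratio is already about 1.03–1.07 with no site effect (0.0406/0.0394; 0.0407/0.0381).
- The empirical SD of the risk difference is the same with and without adjustment (for example 0.0465 in both). Stratification has already delivered the precision; what changes is the reported error.
- False-positive rate, site odds ratio 5: 3.7–4.6% unadjusted, 4.5–6.2% adjusted, with simulation error of about 0.6 points.

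Power at 10% versus 25%:

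| Site odds ratio | Midvale share | Arm only | Arm + site + sex |
|---|---|---|---|
| 2 | 20% | 80.7% | 81.1% |
| 2 | 50% | 81.6% | 82.3% |
| 5 | 20% | 81.9% | 84.7% |
| 5 | 50% | 80.9% | 83.7% |

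**4. Log-odds-ratio scale.** At 10% versus 25% and a site odds ratio of 5, adjustment raises the SE from 0.433 to 0.452 (20% share) or 0.446 (50% share). The estimate moves from about 1.15 to 1.26 or 1.24. Power rises because the conditional odds ratio lies further from 1, not because its interval narrows.

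**5. Sparse control events.** Expected control enrollees: 0.02 × 80 = 1.6. The chance of none is 0.98^80 = 0.199, so in about one trial in five the ordinary odds ratio is not finite, with or without the strata.

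**The case against.** The strongest reply is that this is a condensed article. It never says that the strata are excluded from the model, and a covariate list may stand in an analysis plan that is not shown. That part stands: a reader might infer that the trial will analyse without the strata, and the article does not establish it. But it is not merely silent. It states a covariate rule, and that rule as written handles the design factors poorly.

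A second reply is that the harm is small and rests on assumptions. This also stands. Three stronger readings go too far:

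- *Health system is a strong predictor.* No enrollment rate by site or sex is given. Insurance cover, scholarships and possible access to the free program soften the cost contrast, mainly for the patients most exposed to the fee.
- *The gain equals 6–15% more participants.* That follows only from assumed site rates. Equal sites at 20% and 50% give 0.205 versus 0.2275 (9.9%); a 70/30 split at 25% and 50% gives 6.0%, and at 20% and 60% gives 15.4%. These imply site odds ratios of 4, 3 and 6, and describe variance within an intervention arm only. The Contingency Plans section also calls Midvale the smaller site, which argues against equal shares.
- *The planned odds-ratio intervals are too wide and adjustment would narrow them.* Step 4 shows that adjustment widens the log-odds-ratio interval slightly.

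**Conclusion.** The point holds as a modest matter of precision and specification, not as an error of validity. The design stratifies on two factors, the stated primary model names neither, and the imbalance-triggered weighting would not reliably include them.

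If health system predicts enrollment, the unadjusted analysis is mildly conservative. The risk-difference SE is overstated by roughly 0–8% at an assumed site odds ratio of 5, and part of the upper end reflects how the simulation treated runs without control enrollees. The power lost is about 0.4–0.7 points at a site odds ratio of 2 and about 2.8 points at 5, for assumed rates of 10% versus 25%. With no site difference nothing is lost. At the design rates of 2%, 32% and 45%, power stays above 99% either way, so the point matters only if effects fall well short of the pilot results. Site shares and site effects are assumptions throughout.

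**What to change.** State that health system and sex, as recorded at randomization, are covariates in the primary logistic model for both enrollment and engagement, whether or not baseline imbalance is seen. Fixing the stratum at randomization matters because University patients may attend the Midvale program or supplement the Midvale sample, so health system could otherwise be coded in more than one way.

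Use a penalised (Firth-type) fit, since about 1.6 control enrollees are expected. The sparse control arm calls for this even without the strata.

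A standardized risk difference against best practice, with a variance that reflects the strata, can be reported alongside. The precision gain shows on that scale.

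The cost is about one sentence in the analysis plan. Both variables are already needed for allocation, so no new data are collected. The small downside is that the odds ratio becomes conditional on the strata and should be labelled so.
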